### Protocol Development

#### Intervention Group: Therapist-Facilitated VR Treatment

The objective of the VR intervention is to facilitate the relearning of safety in social events among young individuals. The VR intervention involves the implementation of repeated behavioral experiment tests, which aim to assist participants in realizing that their level of safety is higher than their initial perception. All intervention sessions will be delivered by credentialed mental health professionals who meet the following criteria: (1) each therapist will have completed systematic training in cognitive behavioral therapy (CBT) and will have used CBT as their primary clinical modality for a minimum of 1 year; (2) all therapists will hold a master’s degree in clinical psychology, counseling psychology, or social work and maintain an active professional license or registration in their respective jurisdiction; (3) a registered clinical supervisor, possessing at least 8 years of postqualification experience, will oversee the entire treatment process, provide weekly case consultations, and conduct random session audits to ensure fidelity; and (4) an intervention manual will be developed to standardize session structure, therapeutic techniques, and VR scenario use; therapists will complete manual-based training and must demonstrate competency in role-play assessments before treating study participants. The therapists will take charge of the following 3 key phases of the intervention process:

Intake interview: the mental health worker will assess dysfunctional assumptions and safety behaviors to identify each participant’s key cognitive patterns, allowing VR exposure and cognitive restructuring to be tailored to their most relevant fears and defenses.Document establishment: the mental health professional will establish documentation for each participant, which serves to enhance the efficacy of subsequent VR sessions by allowing the mental health professional to better prepare for participants’ responses and provide more targeted guidance. Furthermore, this documentation will also serve as a means to track and record participants’ progress throughout the trial.VR session preparation: the mental health professional will assist participants in preparing for the VR sessions. This involves guiding individuals through the intervention process, which includes helping them recognize and address dysfunctional thinking styles, encouraging them to put aside maladaptive defense strategies, conducting debriefing sessions at the conclusion of each session, and providing feedback to tailor the progression of each participant. The mental health professional will also encourage participants to apply the learning from VR into the real world through homework tasks to be carried out between sessions.

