### Recruitment

The trial will enroll 90 participants, allocating 45 to each arm. Allowing for 15% attrition, this sample provides 90% power to detect a treatment effect at T1, assuming an independent samples 2-tailed *t* test, an *α* level of .05, and Cohen *d* of 0.75. The target size also accords with comparable 2-arm VR intervention studies [16].

The first participant was enrolled in March 2026. The study will recruit participants from various settings in Hong Kong, including middle schools, tertiary institutions, and community centers. Adequate participant enrollment will be facilitated through partnerships with collaborating institutions, which will post digital flyers and promotional videos on their social-media platforms to reach the target population. The participants’ inclusion criteria were as follows: youth aged 15 to 25 years with a score of 25 or higher on the Social Phobia Inventory (SPIN). The exclusion criteria were as follows: (1) inability to attempt a baseline assessment (eg, due to being unpermitted to leave a psychiatric ward); (2) photosensitive epilepsy or significant visual, auditory, or balance impairment; (3) currently receiving another intensive psychological intervention; (4) a history of neurological conditions (eg, traumatic brain injury); and (5) insufficient language proficiency to understand the intervention requirements. In this trial, any endorsement of suicidal ideation will trigger crisis intervention procedures. Participants will be promptly flagged, and a trained clinician will notify the school or guardian to ensure appropriate safety measures are taken. School tutors or social workers familiar with students’ mental health will help identify participants unsuitable for the study, especially those whose conditions may be masked in self-report questionnaires. Participants will be recruited and screened online or offline, but will complete all interventions offline. Participants will be briefed through tutorial video clips demonstrating the research flow regarding intervention procedures, timing, and frequency.

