### Statistical Analysis

#### Primary Analysis

The primary analysis will follow the intention-to-treat principle, meaning that all randomized participants will be analyzed according to their assigned groups regardless of intervention adherence, withdrawal, or protocol deviation. Between-group differences in SPIN scores at 1-month posttreatment and 3-month follow-up will be examined using linear mixed effects models. The model will include group, time, and the group-by-time interaction as fixed effects, baseline SPIN score as a covariate, and a participant-specific random intercept to account for repeated measurements. The data will be automatically generated by Google Forms once participants complete their responses. A *P* value of less than .05 will be used as the level of statistical significance.

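### The primary model has no term for therapist, although only the VR arm is treated by shared therapists; if therapists differ, the standard error of the group contrast is too small and the 5% test too liberal

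*Protocol article*

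**What the plan says.** **Delivery.** Under Intervention Group: Therapist-Facilitated VR Treatment, the protocol article says "All intervention sessions will be delivered by credentialed mental health professionals" and sets criteria for therapists in the plural. They carry out the intake interview, prepare participants for VR, debrief them, tailor feedback and set homework. Structure of Each Intervention Session gives 10 to 20 minutes of warm-up and 20 minutes of debriefing with the therapist, around a 30-minute VR block that runs without one.

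**Control.** Under Control Group: Waitlist Control, access to the intervention is withheld until after the 3-month assessment. Both outcome time points therefore compare a therapist-treated arm with an arm that has no therapist.

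**Analysis.** Primary Analysis fixes the model: group, time and their interaction, with "baseline SPIN score as a covariate, and a participant-specific random intercept to account for repeated measurements". No other random effect is named. Therapist is also absent from the optional variables under Covariates and Potential Confounding Variables.

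**Power.** Recruitment says "Allowing for 15% attrition, this sample provides 90% power to detect a treatment effect at T1", "assuming an independent samples 2-tailed" t test, and "Cohen *d* of 0.75".

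The article does not give the number of therapists, their caseloads, how participants are assigned to them, or an ICC.

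**The concern.** This is a partially nested design: outcomes may be correlated within therapist in one arm and are independent in the other. The true variance of the VR mean includes a between-therapist part that shrinks with the number of therapists, not the number of participants. A model with only a participant intercept leaves that part out.

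At stake is the validity of the primary test at P<.05 and the width of the intervals at 1 and 3 months. The waitlist section also says that the trial's estimates should inform later sample sizes, so an understated standard error would carry forward.

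This is more than a detail left to an analysis plan. The article itself specifies the random-effects structure, and that structure does not match the delivery it describes.

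**Working it through.** **Inputs from the article (Recruitment).** 45 per arm ("The trial will enroll 90 participants, allocating 45 to each arm"); 15% attrition; standardised difference d = 0.75; two-sided 5% level. Analysed per arm: n = 45 × 0.85 = 38.25.

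**Assumptions, not in the article.** K = 3 to 6 therapists with equal caseloads; each VR participant stays with one therapist; ICC (ρ) of 0.02, 0.05 or 0.10; total variance 1 in each arm.

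**Step 1: reproduce the stated power.** The noncentrality is 0.75 × √(38.25/2) = 3.280. Normal approximation: Φ(3.280 − 1.960) = 0.907. Noncentral t: 0.899. With 38 per arm the values are 0.905 and 0.897. The 90% reproduces under independence, with almost no slack.

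**Step 2: standard error under partial nesting.** The design effect in the VR arm is DE = 1 + (n/K − 1)ρ; in the waitlist arm it is 1. The true standard error divided by the independence standard error is f = √[(DE + 1)/2].

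Example, K = 3, ρ = 0.05: DE = 1 + (12.75 − 1) × 0.05 = 1.587, so f = √(2.587/2) = 1.137.

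**Step 3: actual size when therapist is ignored.** Size = 2[1 − Φ(1.960/f)]. In the example, 2[1 − Φ(1.723)] = 0.085.

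| Therapists (assumed) | ICC 0.02 | ICC 0.05 | ICC 0.10 |
|---|---|---|---|
| 3 | 6.4% | 8.5% | 12.0% |
| 4 | 6.0% | 7.5% | 10.1% |
| 6 | 5.6% | 6.6% | 8.2% |

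A simulation of the unadjusted t test (38 per arm, 40,000 runs) agrees: at ICC 0.05 the size is 8.5%, 7.4% and 6.5% for 3, 4 and 6 therapists.

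**Step 4: does baseline adjustment help?** Assume a baseline-outcome correlation of 0.5, so the residual variance is 0.75, with n = 38, K = 4, ρ = 0.05 and therapist variance unaffected by baseline.
- True variance: (0.75 − 0.05)/38 + 0.05/4 + 0.75/38 = 0.0507.
- Variance under independence: 2 × 0.75/38 = 0.0395.
- f = √(0.0507/0.0395) = 1.133, and size is 8.4%, against 7.5% without adjustment.

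Adjustment removes residual variance and leaves the therapist part, so the relative understatement grows.

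**Step 5: what happens to power.** Two different tests must be kept apart.
- *Unadjusted t test that ignores therapist.* Its rejection probability at d = 0.75 is Φ[(3.280 − 1.960)/f]: 0.877, 0.885 and 0.892 for 3, 4 and 6 therapists at ICC 0.05, and 0.894 to 0.901 at ICC 0.02. It loses about 1 to 3 points at ICC 0.05. Its defect is size.
- *Test that accounts for therapist.* With therapist variance treated as known, power at ICC 0.05 is Φ(3.280/f − 1.960) = 0.822 to 0.869 for 3 to 6 therapists. With Satterthwaite degrees of freedom (K − 1 for the VR arm) it is about 0.65, 0.75 and 0.82 for 3, 4 and 6 therapists, on about 5 to 15 df.

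**The case against.** The strongest reply has four parts.

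- **Standardisation.** The article provides a manual, role-play competency checks, one supervisor overseeing all treatment, weekly consultation and random audits, and the exposure block runs without the therapist. These favour a low ICC, and at ICC 0.02 the excess size is about one point. This stands as a reason for proportion. It does not make the ICC zero, and the article does not claim that it does.
- **Power.** A reader might infer that the stated 90% is wrong, or that the trial is underpowered. The article does not support that. It states its assumption openly, an independent-samples t test, and under it the figure reproduces. The planned model also adjusts for baseline SPIN, which the power statement ignores. With an assumed correlation of 0.5 and ICC 0.05, power allowing for therapist is 0.915 with 4 therapists and 0.945 with 8 (normal approximation), or 0.827 and 0.923 with small-sample df. Whether the planned analysis falls below 90% cannot be settled from the article.
- **Estimability.** With few therapists the between-therapist variance is barely estimable. This stands, and it is why the fix allows a sensitivity analysis and a fallback.
- **Early-stage trial.** The article calls its evidence preliminary. It still tests at P<.05, so the size of that test matters.

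**Conclusion.** The point holds in conditional form. The design is partially nested and the specified primary model omits therapist. If the therapist ICC exceeds zero, the standard error of the group contrast is too small at both time points and the nominal 5% test is too liberal. With 3 to 6 therapists the actual size is about 5.6 to 6.4%, 6.6 to 8.5% and 8.2 to 12.0% at ICC 0.02, 0.05 and 0.10. Therapist number, equal caseloads and ICC are all assumptions, and at the low end the effect is small. Baseline adjustment does not repair it.

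The conclusion does not extend to a definite loss of power. All that can be said of the 90% is that it rests on independent participants and allows nothing for therapist clustering.

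**What to change.** Keep N at 90 and make three changes.

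1. **Record the treating therapist** for every VR participant, and state the number of therapists and the assignment rule. Recruitment reports the first enrolment in March 2026, so the field should be captured now.
2. **Prespecify a partially nested analysis**: a therapist random effect that applies in the VR arm only (waitlist participants as singletons), with small-sample degrees of freedom such as Kenward-Roger. It may be the primary or a sensitivity analysis. If there are too few therapists to estimate the variance, report the T1 and T2 effects with standard errors recomputed at ICC 0.02, 0.05 and 0.10.
3. **Qualify the power sentence in Recruitment**: say that the 90% assumes independent participants and makes no allowance for therapist clustering. Do not substitute a figure such as 82 to 87%. That range treats the therapist variance as known, whereas the recommended model must estimate it, which gives about 65 to 82% on the same inputs before any gain from baseline adjustment.

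The cost is one data field and one model term, wider intervals, and few degrees of freedom if therapists are few.

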#### Theoretical Framework

This research will use Clark and Wells’s cognitive model of social phobia (Figure 2) [11]. This model identifies the following 4 key processes that maintain social avoidance [12]:

Social situation: for adolescents, commonplace events such as giving a short class presentation constitute highly salient “social situations” that can trigger the Clark-and-Wells cycle; epidemiological work shows that such youth-relevant contexts frequently precipitate the first onset of social anxiety [17].Activates assumptions: exposure to these situations activates developmentally tuned self-rules. Assumptions such as “If I look awkward, my peers will screenshot and mock me” are shaped by heightened peer sensitivity during adolescence. These maladaptive assumptions prime threat detection systems and lower the threshold for anxiety activation [18].Perceived social danger (negative automatic thoughts): the activated rules generate rapid thoughts such as “My hands are shaking—everyone will notice,” inflating both the probability and the cost of negative peer evaluation [19].Processing self as a social object: attention turns inward; the adolescent continuously monitors facial redness, voice quiver, or online “likes,” embodying the self as an observable object. This self-focused processing amplifies somatic and cognitive symptoms (eg, tachycardia, blanking) while prompting safety behaviors, such as looking down, muting the mic, and overediting photos, that temporarily soothe anxiety yet block disconfirmation of catastrophic beliefs [20].

**Figure 2. F2:**
[figure not shown]
Cognitive model of social anxiety disorder used in this study.

#### Intervention Design and VR Scenarios

The intervention comprises 6 sessions of 60 minutes each. This structure could be effective and practical for the target demographic in Hong Kong, considering the efficacy of brief interventions, challenges with longer program retention, and the need for adaptability to the local context [21]. There are 6 VR scenarios: a café, classroom, interview room, public bus, social gathering, and family gathering. Each scenario consists of 10 sequentially structured tasks, increasing in difficulty over time. For example, in a job interview scenario, task 1 involves the participant interacting with a friendly interviewer. Task 2 introduces a neutral, more serious interviewer. Task 3 features a foreign language–speaking interviewer, requiring the participant to respond in a nonnative language (eg, English). Before each task, participants will see an automated dashboard through the VR headset, providing background information and clear instructions on required actions, such as introducing themselves by saying, “Hello, my name is Chan Da Men.” To enhance engagement and support, the system monitors response time and, if no response is detected within 20 seconds, automatically displays assistance options, including taking a short break, requesting support from a psychologist, or extending response time. This structured approach ensures that participants receive gradual exposure, real-time guidance, and adaptive support, enhancing learning, confidence, and anxiety management in the VR intervention.

The ecological validity of the scenarios was strengthened through pilot interviews with youth who reported elevated social anxiety symptoms, as well as consultations with local mental health professionals and a parent (see the “Pilot Study” section for more details). The selected scenarios were chosen because they reflect common social and performance-based contexts encountered by youth in Hong Kong, including classroom participation, public speaking, job or school interviews, commuting and public transport interactions, peer gatherings, café or casual social encounters, and family gatherings. These situations were considered developmentally relevant because adolescents and young adults in Hong Kong often face intense academic expectations, bilingual or multilingual communication demands, dense public social environments, and frequent evaluation in school, university, and early-career settings. The VR tasks within each scenario were therefore designed to reflect locally recognizable interpersonal demands rather than generic exposure tasks. Examples include responding to questions from teachers or interviewers, initiating or maintaining conversations with peers, managing attention from others in public spaces, and coping with perceived evaluation during group or family interactions. This culturally and contextually informed design aims to improve the relevance and acceptability of the intervention for Hong Kong youth while maintaining a standardized structure for trial delivery.

#### Intervention Flow

##### Structure of Each Intervention Session

Before each of the 6 intervention sessions, participants can freely choose from the 6 available VR scenarios based on their personal preferences and therapeutic needs. Each session is structured into 3 key phases (intervention flowchart; Figure 3):

Warm-up (10‐20 min): in the first session, therapists introduce themselves, provide an overview of the 6-session intervention, explain procedures and safety precautions, and address participants’ questions and concerns to build rapport. From the second to the sixth session, therapists review the chosen scenario, reflect on the previous session, and conduct a homework check-in to reinforce learning and progress.VR intervention (30 min): participants move to a separate VR-equipped room, where they wear a VR headset and a smartwatch to track physiological indicators, while a camera records real-time responses for later video feedback analysis. During the 30-minute session, the intervention runs autonomously without therapist assistance. Therapists remain in a monitoring room, receiving real-time feedback on participants’ body movements, voice volume, reaction speed, and fluency, as well as physiological indicators (eg, heart rate and skin conductance). If needed, therapists are on standby to enter the participant’s room on request.Debriefing (20 min): after the VR session, participants and therapists review the experience using video feedback and physiological data, identifying specific challenges, such as self-focused attention or cognitive distortions contributing to social anxiety. Therapists introduce coping strategies, such as deep breathing, to help manage anxiety in real-world situations. Before concluding the session, participants receive simple homework assignments, such as practicing breathing exercises in daily social interactions to reinforce learning and real-life application.

**Figure 3. F3:**

Intervention flowchart of the virtual reality (VR) program.

##### Intervention Feature 1: Wearable Watch for Real-Time Biological Data Collection

To enhance real-time monitoring of participants’ mental states during the intervention, a commercially available wearable health-monitoring device will be used to collect physiological indicators, including: (1) electrodermal activity (EDA), which reflects changes in skin conductance and indicates levels of physiological arousal and emotional responses; and (2) heart rate variability (HRV), which measures variations in heartbeats associated with stress and emotional regulation. These physiological markers offer objective indicators of anxiety and emotional responses during VR-based exposure tasks.

The collected data will be transmitted in real-time to the back-end control panel (CP), allowing the research team to monitor participants’ anxiety responses during different VR scenarios. If the system detects elevated physiological responses (eg, increased EDA or decreased HRV) during a specific VR task, it signals that the participant may be experiencing heightened anxiety. The biological data will be reviewed postsession with the counseling psychologist. During follow-up discussions, the CP will explore the participant’s experience, validate their emotional responses, and help them develop personalized coping strategies based on their reactions.

##### Intervention Feature 2: AI-Driven Adaptive Support and Ethical Safeguards

During sessions, AI-driven interactive support was provided through Doubao (developed by ByteDance), an AI-powered large language model used in this study primarily for speech recognition and response detection. Based on predefined indicators such as task progression, response delay, and physiological arousal patterns, the system may provide brief and standardized prompts. If signs of frustration, distress, elevated arousal, or prolonged nonresponse are detected, the AI adjusts its approach by offering reassurance, motivational feedback, or brief reminders to use breathing or grounding strategies introduced by the therapist. The AI component is used as a lightweight supportive function; it does not provide diagnoses, make clinical decisions, assess risk independently, or replace therapist judgment. Moreover, after each VR session, Doubao AI generates a personalized postsession report summarizing the participant’s emotional and physiological responses, as well as task completion. The report highlights moments of peak anxiety and recommendations for the next session, including areas for improvement and potential adjustments to intervention difficulty or pacing. Any AI-generated feedback used in debriefing will be reviewed by the therapist, who will decide whether and how to incorporate it into the session discussion. Prompts and feedback templates will be reviewed by the research team to ensure that they are clinically appropriate, nonjudgmental, and consistent with the intervention manual. The back-end code and implementation details can be made available upon reasonable request.

To protect data privacy, identifiable participant information will not be included in AI-generated summaries. Study data will be coded using participant IDs, and access to identifiable data will be restricted to authorized research personnel. Data transmission and storage will follow the approved data security procedures described in the ethics application. Participants will be informed during the consent process that AI-supported feedback may be used as part of the intervention, the type of data involved, the purpose of the AI-generated feedback, and the limits of AI involvement.

